**Methods:**

The Intramuscular Diamorphine versus Intramuscular Pethidine (IDvIP) trial is a randomised double-blind two centre controlled trial comparing intramuscular diamorphine and pethidine regarding their analgesic efficacy in labour and their side effects in mother, fetus and neonate. Information about the trial will be provided to women in the antenatal period or in early labour. Consent and recruitment to the trial will be obtained when the mother requests opioid analgesia. The sample size requirement is 406 women with data on primary outcomes. The maternal primary outcomes are pain relief during the first 3 hours after trial analgesia and specifically pain relief after 60 minutes. The neonatal primary outcomes are need for resuscitation and Apgar Score <7 at 1 minute. The secondary outcomes are an additional measure of pain relief, maternal sedation, nausea and vomiting, maternal oxygen saturation, satisfaction with analgesia, whether method of analgesia would be used again, use of Entonox, umbilical arterial and venous pH, fetal heart rate, meconium staining, time from delivery to first breath, Apgar scores at 5 mins, naloxone requirement, transfer to neonatal intensive care unit, neonatal haemoglobin oxygen saturation at 30, 60, 90, and 120 mins after delivery, and neonatal sedation and feeding behaviour during first 2 hours.

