• *Fetal Monitoring*. Fetal well-being will be monitored by continuous monitoring of fetal heart rate baseline and variability according to standard department protocols and classified as **Reassuring **(baseline 110-160 bpm, variability >5 bpm, no decelerations and accelerations present); **Non-reassuring **(baseline 100-109 or 161-180, variability of <5 for >40 but <90 minutes, and early or variable decelerations or a single prolonged deceleration up to 3 minutes) or **Abnormal **(Baseline <100 or >180 or sinusoidal pattern for >10 minutes, variability of <5 for >90 minutes, and atypical variable decelerations or late decelerations or a single prolonged deceleration of greater than 3 minutes). CTG monitoring is made using Corometrics 170 series machine in PHFT and using the Phillips PN/2703A machine at RUH. If meconium staining occurs then the time of first appearance in relation to administration of trial drug will be noted. At delivery cord blood will be taken for measurement of umbilical arterial and venous pH.

• *Neonatal Monitoring*. Neonatal condition will be assessed by time to first breath, Apgar score at 1 minute and 5 minutes, need for naloxone, need for resuscitation by bag mask ventilation or intubation and transfer to Neonatal Intensive Care Unit (NICU). Neonatal oxygen saturation will also be measured every 30 minutes from birth for 2 hours using the Masimo Rad 5 pulse oximeter at PHFT and Mindray PM-60 at RUH. Neonatal sedation in the first 2 hours of life will also be recorded using the same scoring system as the parturient. Time from delivery to first feed will be recorded as well as a subjective assessment of feeding behaviour by the midwife (0 = normal; 1 = mildly depressed rooting and sucking behaviour; 2 = severely depressed rooting and sucking behaviour) during the first 2 hours of life.

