##### Other

(e) Maternal sedation score over first 3 hours

(f) Time from first dose to delivery

(g) Entonox or regional analgesia given

(h) Nausea over 3 hours

(i) Vomiting over 3 hours

(j) Oxygen saturation over 3 hours after each dose of study drug or until delivery

(j) Percent reporting that they would choose the same pain relief in their next pregnancy

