#### Neonatal

(a) Cardiotocography over the first 3 hours after each dose of study drug or until delivery

(b) Time from first dose to first meconium staining

(c) Umbilical artery pH and vein pH

(d) Time from delivery to first breath

(e) Apgar score at 5 mins

(f) Requirement for naloxone

(g) Neonatal oxygen saturation at 30 mins, 60 mins, 90 mins, 120 mins after delivery

(h) Time from delivery to first feed

(i) Feeding behaviour during first 2 hours

(j) Neonatal sedation in the first 2 hours after delivery

(k) Transfer to neonatal intensive care unit

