Supplementary analyses will adjust for the following covariates that might have an impact on primary outcomes: maternal age, parity, gestation, pre-administration pain intensity. No formal correction for multiplicity will be applied to the significance tests for the 4 primary outcomes. Under the null hypothesis that the two treatment groups give identical outcomes, the probablities of 1 or more, 2 or more, 3 or more, or all 4 being statistcally significant are 0.19, 0.01,<0.001 and <0.001 respectively. The trial report will include a section on the impact of multiplicity on interpretation of the results.

Analysis of secondary outcome measures is likely to be as follows. The distributions of oxygen saturation and nausea VAS are likely to be highly skewed and so values will be categorised. For example, as under 95, 95-97, 98-100 for oxygen saturation and 0, 0.1-4.9, 5+ for nausea. These and other repeated measures categorical outcomes (verbal pain intensity, pain relief, maternal sedation, vomiting, cardiotocography) will be analysed in two ways; (a) using repeated measures models, and (b) as the proportion of women having a poor result during the 3 hour follow-up, using logistic regression (eg proportions having oxygen saturation 97 or below, nausea 5+, verbal pain intensity moderate or worse, pain relief none or slight, sedation moderate or severe, vomiting, cardiotocography non-reassuring or abnormal). Neonatal oxygen saturation and sedation scores in the 2 hours after delivery will be analysed using a similar approach.

Maternal satisfaction with analgesia and neonatal feeding behaviour (normal, mildly depressed, severely depressed) will be analysed using multinomial logistic regression.

Dichotomous outcomes such as Apgar score < 7 at 5 minutes, use of naloxone, transfer to neonatal intensive care unit, and reporting that they would choose the same analgesia for their next pregancy, will be analysed using logistic regression.

Time from first administration of study drug to delivery, and time to first meconium staining (excluding those where staining ocurred prior to trial drug), and time from delivery to first feed and time to first breath will be analysed using proportional hazards models, and the results presented as hazard ratios.

Multiple regression will be used to analyse umbilical artery pH and vein pH. Results will be presented with 95% confidence intervals whenever possible.

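### Meconium staining is compared only as an hourly hazard up to delivery, so if one opioid lengthens labour the result does not show whether more babies are stained

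*Protocol article*

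**What the plan says.** The Abstract (Methods) lists the outcome with no time element: "fetal heart rate, meconium staining, time from delivery to first breath". Under Secondary outcome measures, Neonatal, item (b), it becomes "Time from first dose to first meconium staining". The Statistical Analysis section groups it with three other time outcomes: "time to first meconium staining (excluding those where staining ocurred prior to trial drug") and the rest "will be analysed using proportional hazards models, and the results presented as hazard ratios".

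The data for a different analysis are collected. Under Measurements, Fetal Monitoring: "If meconium staining occurs then the time of first appearance in relation to administration of trial drug will be noted". Logistic regression is planned for "Dichotomous outcomes such as Apgar score < 7 at 5 minutes, use of naloxone, transfer to neonatal intensive care unit" and similar outcomes, but staining is not named there. The maternal secondary outcomes include, as item (f), "Time from first dose to delivery", so the interval during which staining can be seen is itself compared between arms.

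**The concern.** A labour in which the liquor stays clear stops being at risk of staining at delivery. In an ordinary proportional hazards model that woman is censored at delivery. The null hypothesis is then an equal hourly rate of first staining among women not yet delivered. That differs from an equal proportion of stained babies unless the drugs leave the dose-to-delivery interval unchanged.

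If one drug lengthens labour, three things follow:

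- With the same proportion stained, the extra undelivered hours push that drug's hazard ratio below 1, so it looks protective.
- A true excess of stained babies in that arm is pulled towards a hazard ratio of 1.
- With the same hourly rate, the slower drug leaves more babies stained while the hazard ratio stays at 1.

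The trial sets out to compare side effects in mother, fetus and neonate. For this fetal sign, the one stated comparison could favour the labour-prolonging drug or miss an excess.

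**Working it through.** **Inputs.** The article gives no staining rate, no dose-to-delivery interval and no power figure for this outcome, so there is no stated figure to reproduce. From the article: two-sided 5% significance; 203 per group needed, and 450 to be recruited (450/2 = 225 per arm). Everything else below is assumed. Excluding women stained before dosing would reduce the numbers somewhat.

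**Rough algebra.** Let *p* be the proportion stained and *T* the mean time at risk per woman. The crude rate ratio is (p1/T1)/(p0/T0) = (p1/p0) × (T0/T1).

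- Equal risk, with 4 h v 5 h at risk: 1 × 4/5 = 0.80.
- True excess of 15% v 26%: 26/15 = 1.73, and 1.73 × 4/5 = 1.39.

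The labour effect enters the ratio directly, whatever happens to the babies.

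**Simulation 1.** 225 per arm, 4,000 trials per scenario. Dose-to-delivery is lognormal, median 4 h in one arm and longer in the other, log-SD 0.7. Each labour has a fixed staining risk, with onset either even over the interval or in its last third. A log-rank (Cox score) test with censoring at delivery is compared with a two-sample test of proportions. Cells show the percentage of trials rejecting.

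| Scenario | Hazard test, even onset | Hazard test, last third | Proportions |
|---|---|---|---|
| Equal risk 15% / 25%, +1 h | 8.3 / 11.3 | 17.1 / 27.0 | 4.6–5.3 |
| Equal risk 15–25%, +1.5 h | 13–20 | 30–48 | about 5 |
| 15% v 26%, no labour effect | 81 | 77 | 83 |
| 15% v 26%, +1 h | 57 | 32 | 83 |
| 15% v 26%, +1.5 h | 44 | 16 | 83 |

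In the last two rows the excess is in the slower arm. With equal risk and +1 h, the mean hazard ratio is about 0.87 (even) or 0.78 (last third), in line with the rough 0.80. At +0.5 h the false rejection rate is 6–10%. Repeat runs at +1 h gave 9–12% (even) and 17–29% (last third), so simulation error does not change the picture.

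With a constant and equal hourly hazard instead, 4 h v 5.5 h gives 15% v 20% stained (or 25% v 32%). The mean hazard ratio is 1.0, the hazard test rejects in 5%, and the proportions test in 27% (or 38%).

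**Simulation 2, different model.** 203 per group, 3,000 trials. Dose-to-delivery is gamma with shape k = 2 and mean m. With a constant hourly hazard λ, P(stained) = 1 − (1 + λm/k)^(−k).

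- Setting m = 4 and P = 0.15 gives λ = 0.0423.
- At m = 6: 1 − (1 + 0.0423 × 6/2)^(−2) = 1 − 1.1269^(−2) = 0.213.
- Simulated with equal hourly rates and labour 2 h longer: 15.0% v 21.2% stained, hazard ratio 1.00, Cox rejects in 5%, proportions test in 37%.
- Over means of 4 or 6 h, baseline risks of 10–20% and shapes of 1.5–3, the 2 h longer arm gains 3 to 8 percentage points of stained babies while the hazard ratio is 1 by construction.
- Fixed 15% risk in both arms, +2 h, even onset: hazard ratio 0.77. Cox favours the slower drug in 16% of trials (nominal 2.5%).
- 15% v 27%, +2 h, even onset: hazard ratio 1.47. Cox power is 37%, against 86% for proportions.
- With no labour effect and equal risk, both tests hold their level (Cox 4–5%, proportions 4–5%).

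**The case against.** The strongest reply is that the article never says women are censored at delivery. A subdistribution hazards model, with delivery as a competing event, is also a proportional hazards model. Under the assumptions of Simulation 1 it rejects in 4.6–5.5% of equal-risk trials and has 79–84% power for 15% v 26%, so it avoids the problem. That reading is possible but not the natural one. The sentence covers four time outcomes together, names no competing event, and the named software is SPSS and MLWin. Read plainly, it yields an ordinary Cox model.

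Second, the secondary analyses are introduced as likely, and the list for logistic regression is illustrative, so a comparison of proportions is not excluded. That is true, but none is stated, and staining is expressly assigned to the hazard model. For vomiting, sedation and cardiotocography, by contrast, the same section adds the proportion of women with a poor result.

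Third, an hourly rate is a legitimate quantity, it fits the outcome as listed, and the separate analysis of time to delivery would show a labour effect. This stands as a reason to keep the hazard ratio. It does not tell the reader whether more babies were stained.

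Fourth, nothing in the article shows that either drug lengthens labour relative to the other, and the largest figures need both a long delay and late onset. This stands in full: the harm is conditional, and it limits the weight of the point.

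**Conclusion.** The concern holds, conditionally on a difference in labour length. As written, the meconium analysis answers whether more babies are stained only if the drugs do not affect the dose-to-delivery interval, which the trial itself sets out to compare.

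Under the assumed inputs, a 1 h difference raises the false rejection rate from 5% to between 8% and 27%, and cuts power for a 15% v 26% excess from 83% to 57% or 32%, depending on when staining appears. With no difference in labour length the two analyses nearly agree (77–81% v 83%). The direction of the distortion follows from the definitions; its size depends on assumed staining rates, intervals and onset patterns. This is a secondary outcome and the primary conclusions are unaffected, but the result could point the wrong way on fetal harm, so the change should be made.

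**What to change.** In the Statistical Analysis section, make the between-group analysis of meconium staining the proportion of women with new staining between first dose and delivery. Use logistic regression controlling for site, keep the existing exclusion of women stained before the trial drug, and report an odds ratio and a risk difference with 95% confidence intervals. If timing is still of interest, show cumulative incidence curves with delivery as a competing event. Report the hazard ratio only as a supplementary hourly rate, read beside the time-to-delivery result.

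The cost is about one sentence. Occurrence and time of staining are already recorded, and the same model is already planned for other dichotomous outcomes. The one concession is that timing becomes supplementary; power is about the same if labour length does not differ between arms.

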## Retention of Data Records and Data Protection

Data records will be kept in a secure locked cupboard for a period of 30 years. All data will be held on RUH and PHFT computers, which are password protected. The data on computers will be anonymised and comply with the Data Protection Act.

## Adverse Event Reporting

### Definitions

An **Adverse Event (AE) **is defined as any untoward medical occurrence or experience in a patient or clinical investigation subject which occurs following the administration of the trial medication regardless of the dose or causal relationship. This can include any unfavourable and unintended signs or symptoms, an abnormal laboratory finding or a disease temporarily associated with the use of the protocol treatment whether or not related to the medicinal product. For example:

• any new diagnosis

• any symptom that requires medicinal clarification or leads to in-patient admission

• any suspected adverse drug reaction

• any symptom that appears on the participant's medical records

• any event related in time with the intake of the study medication and affecting the health of the participant (including laboratory value changes)

### Adverse Event Severity (AEs)

All AEs will be examined to determine severity. The intensity of an AE, as assessed by the investigator, will be recorded as either 'mild', 'moderate' or 'severe', as indicated by the following definitions:

• *Mild*: an event that requires minimal clinical treatment, or an AE requiring monitoring but no intervention or treatment; causes slight discomfort

• *Moderate*: an event that requires non-routine intervention; i.e. a new clinical treatment or diagnostic procedure, administered within an hour of the event; causes annoying discomfort.

• *Severe*: incapacitating with inability to do usual activities or significantly affects clinical status, and warrants intervention.

### Relationship of the Adverse Event to Study Treatment

An AE is considered associated with the use of the drug if the attribution is classified as "Possible", "Probable" or "Very Likely".

Causality definitions

**Unrelated**: There is sufficient information available to show that the aetiology is unrelated to the drug.

**Unlikely**: An AE for which an alternative explanation is more likely (e.g. concomitant medications, concomitant diseases), and/or the relation with time suggests that a causal relationship is unlikely.

**Possible**: An AE which might be due to the use of the drug. An alternative explanation (e.g. concomitant medications, concomitant diseases) is inconclusive. The relationship in time is reasonable; therefore the causal relationship cannot be excluded.

**Probable**: An AE which might be due to the use of the drug. The relationship in time is suggestive. An alternative explanation is less likely (e.g. concomitant medications, concomitant diseases).

**Very likely**: An AE, which is listed as a possible adverse reaction and cannot be reasonably, explained by an alternative explanation (e.g. concomitant medications, concomitant diseases). The relationship in time is very suggestive.

**Adverse Drug Reactions (ARs) **are responses to a drug which are noxious and unintended and which occur at doses normally used in man for prophylaxis, diagnosis, or therapy of diseases or for modification of physiological function. An adverse 'reaction', contrary to an 'event' is characterised by the fact that a causal relationship between the drug and the occurrence is suspected, i.e. judged possible by the reporting or a reviewing health professional.

An **Unexpected Adverse Drug Reaction **is any adverse reaction for which the nature or severity is not consistent with the applicable product information.

A **Serious Adverse Event (SAE) **is defined as any undesirable experience occurring to the patient, whether or not considered related to the protocol treatment. A **SAE **which is considered related to the protocol treatment is defined as a **Serious Adverse Drug Reaction (SADR).**

A **Suspected Unexpected Serious Adverse Reaction (SUSAR) **is classified as 'unexpected' i.e. a serious adverse reaction, the nature and severity of which is not consistent with the information about the medicinal product in question set out in the summary of product characteristics for the product.

Adverse events and adverse drug reactions which are considered as serious are those which result in death; a life threatening event; prolongation of hospitalisation; persistent or significant disability/incapacity, a congenital anomaly/birth defect; any other medically important condition (i.e. important adverse reactions that are not immediately life threatening or do not result in death or hospitalisation but may jeopardise the patient or may require intervention to prevent any of the other outcomes listed above).

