### Reporting Procedure

The documentation of reporting of SAEs should be in accordance with ICH guidelines for Good Clinical Practice (5.17.1, 5.17.2 and 5.17.3) [17].

All serious adverse events (SAEs) or drug reactions (SDRs) (e.g. allergic reaction) arising from the use of the diamorphine or pethidine occurring from time of randomisation until 30 days after the last protocol treatment administration, will be reported to the following bodies:-

a) MHRA

b) Southampton and South West Hampshire Research Ethics Committee

c) Sponsor (Poole Hospital NHS Foundation Trust) via the local Trust adverse incident reporting form (AIRS form) and also to the Research Governance Departments of the respective Trusts.

d) Chair of the Data and Safety Monitoring Committee

Reporting will be done by fax within 24 hours of the initial observation of the event. The principal investigator will decide if these events are related to the protocol treatment or not. Completed documentation of any reported adverse events or serious adverse drug reactions will be returned within 10 days of the initial report by the principal investigator. SAE will be followed until significant changes return to baseline, the event stabilises or is no longer considered as clinically significant by the investigator, or patient dies or withdraws consent.

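### The seriousness list omits hospital admission, which its own last item presupposes, and the reporting sentence leaves open whether SAEs are reported regardless of cause

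*Protocol article*

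**What the plan says.** Five places in the protocol article bear on this.

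- **Definitions (adverse event).** One example of an ordinary AE is "any symptom that requires medicinal clarification or leads to in-patient admission".
- **Relationship of the Adverse Event to Study Treatment (SAE definition).** An SAE "is defined as any undesirable experience occurring to the patient, whether or not considered related to the protocol treatment". This sentence sets no threshold of seriousness.
- **Same section, closing paragraph (seriousness criteria).** "Adverse events and adverse drug reactions which are considered as serious are those which result in death; a life threatening event; prolongation of hospitalisation", followed by disability or incapacity, birth defect, and other medically important conditions. The last item is explained as "important adverse reactions that are not immediately life threatening or do not result in death or hospitalisation but may jeopardise the patient", or that may need intervention to prevent one of the listed outcomes.
- **Reporting Procedure.** Expedited reporting covers "All serious adverse events (SAEs) or drug reactions (SDRs) (e.g. allergic reaction) arising from the use of the diamorphine or pethidine", from randomisation to 30 days after the last dose. Reports go by fax within 24 hours to the MHRA, the ethics committee, the sponsor and the DSMC chair. The principal investigator then decides whether the events are related to treatment.
- **Documentation of adverse events, and the DSMC section.** AEs are recorded in the CRF, with seriousness coded by the definition above, and the DSMC receives anonymised details of all of them.

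**The concern.** The closing paragraph on seriousness does all the sorting. The SAE definition has no threshold of its own, and CRF coding refers back to it, so a gap in the list carries through to both the coding and the 24-hour report.

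The gap matters in this population. Women are in hospital when dosed, while the reporting window runs to 30 days after the last dose. Once mother and baby have gone home, a serious event may well take the form of a readmission, and that form is not listed.

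The second difficulty is the phrase "arising from the use of the diamorphine or pethidine occurring from time of randomisation until 30 days after the last protocol treatment administration". If it qualifies SAEs as well as drug reactions, someone must judge causality before sending the report, although the same section places the relatedness decision after it. The Statistical Analysis section gives the DSMC's main role as monitoring SAEs, so these two pieces of wording determine which events reach its chair promptly.

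**Working it through.** No arithmetic applies. No sample size, power, alpha or event count depends on this text, so the check is a comparison of wording.

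**Hospitalisation**

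1. The list has six entries: death, life-threatening event, prolongation of hospitalisation, disability or incapacity, birth defect, and other medically important condition. Only the third mentions hospital, and it concerns a stay already under way.
2. The explanation of the sixth entry excludes reactions that "do not result in death or hospitalisation but may jeopardise the patient" from the outcomes already covered. Death is indeed a listed outcome. Hospitalisation is not; only its prolongation is. The list and its explanation do not match.
3. The only other place where admission appears is the AE definition, where it makes an event an AE and not a serious one.
4. Take a readmission on, say, day 10 that is not life-threatening or disabling. It prolongs no current stay, so the third entry fails. Entries one, two, four and five fail by construction. Only the sixth remains. It depends on judgement, and its explanation speaks of adverse *reactions*, a term the protocol keeps for events with suspected causality.
5. The SAE definition refers to the patient and does not say expressly that the baby's events count, so a neonatal readmission is, if anything, less clearly covered.

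**Causality**

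| Text | Points towards |
|---|---|
| SAE definition: "whether or not considered related to the protocol treatment" | reporting regardless of cause |
| Reporting sentence, qualifier attached to SAEs and drug reactions alike | reporting of drug-caused events only |
| Reporting sentence, qualifier attached to drug reactions alone | reporting of all SAEs |
| Relatedness decided by the principal investigator for the reported events | reporting regardless of cause |
| Window opening at randomisation, before any drug is given | reporting regardless of cause |

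The sentence allows both readings. The surrounding text favours the wider one, but a site that takes the narrow reading has a grammatical basis for it.

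**What is at risk**

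An event that misses the SAE route is still to be documented as an AE and passed to the DSMC. What may be lost is the serious label and the 24-hour report to the four recipients.

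**The case against.** The strongest reply has four parts.

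- **The sixth criterion is a backstop.** Its explanation joins its conditions with *or*, so a readmission that is not immediately life-threatening but may jeopardise the patient can qualify. This stands. A reader might infer that every readmission that is not fatal, life-threatening, disabling or a birth defect counts as non-serious; the protocol does not support that. What remains is that such a readmission is serious only by discretion.
- **The omission is probably a drafting slip.** The explanation itself treats hospitalisation as serious. This is accepted, and nothing shows that readmission was excluded on purpose. The slip still needs correcting, because the list is what sites will apply.
- **The protocol does not clearly filter by cause.** A reader might infer that only drug-caused SAEs are reported. The causality-free definition, the later relatedness decision and the opening of the window at randomisation all point the other way. This stands: the sentence is ambiguous and does not set a definite restriction.
- **Nothing goes unreported.** A reader might infer that readmissions or unrelated events vanish from view. The AE documentation and the DSMC's access to all AEs count against that, for both limbs. Only the expedited route is in doubt.

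The ICH sections cited under Reporting Procedure are not reproduced in the article, so they can neither confirm nor cure the gap.

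**Conclusion.** The point holds within limits. The seriousness list is inconsistent with its own last item and leaves readmission of mother or baby outside any hospitalisation criterion during a 30-day window. The reporting sentence is ambiguous, and on one available reading it contradicts the SAE definition and the relatedness step that follows it. The consequence is that some events may be coded as non-serious, or held back from the 24-hour report, and that the two sites may handle like events differently.

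The number of events affected cannot be derived. The protocol aims to recruit 450 women with singleton pregnancies but gives no readmission rate and no time of discharge. That a material part of the 30 days falls after discharge is an assumption. No outcome definition, analysis, sample size, power or alpha changes. The correction is worth making because it is cheap and bears on safety capture.

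**What to change.** 1. **Seriousness criteria** (end of Relationship of the Adverse Event to Study Treatment). Replace the entry on prolongation with: *in-patient hospitalisation (including readmission of mother or neonate) or prolongation of hospitalisation*. The list then agrees with the explanation of its last item, and the baby is named.
2. **Reporting Procedure.** Reword so that all SAEs within the window are reported regardless of presumed causality, in line with the SAE definition. Let the phrase about arising from the trial drugs qualify drug reactions only, and say that relatedness is assessed after the report.

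The cost is a wording amendment and some additional SAE forms, a number the documents do not allow one to estimate. Design and analysis are untouched.
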